### Data management

Participant data will be anonymized and entered into the iCReaT platform created by the Korean government to allow researchers and investigators to input the research data safely and directly. The iCReaT platform is equipped with a web-based encryption system to protect the research data from unauthorized access and disclosure, and it will be accessible only to the principal investigator and designated statistical analysts. The e-CRF system will be used for this clinical trial. The iCReaT will be managed by specialized clinical research coordinators in each hospital and via a contract with a specialized company with extensive experience in eCRF management. For clinical trial monitoring, both on-site and in-house monitoring, using the electronic data capture system will be conducted by designated monitoring researchers.

### Sample size justification

In this trial, 100 participants will be recruited, with 50 in each group. Based on previous studies by Copay et al., the non-inferiority margin is 12.8 points and the maximal clinically accepted ODI difference is 12.8 points, with an SD of 17.1 points at 1-year after endoscopic discectomy [21, 35]. Based on the non-inferiority margin of 12.8, 50 participants will be required in each group, with an alpha value of 0.05, a power of 0.90, a one-sided 95% CI, and a loss to follow-up of 20%. Power Analysis and Sample Size software (version 15; NCSS, Kaysville, UT, USA) was used to calculate the sample size.

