
### Statistical analyses

All statistical analyses will be performed using SAS Enterprise Guide 4 (SAS Institute Inc., Cary, North Carolina, USA). Before performing the main comparative statistical analyses, we will assess whether the baseline variables of the two groups are visually balanced.

An intention-to-treat strategy will be implemented in this non-inferiority RCT. In addition, sensitivity analyses using per-protocol and As-treated will be conducted to identify the deviations from the original assignments during randomization. Participants excluded before or after surgery will not be considered for analysis or replaced, thus avoiding the risk of bias in allocation concealment.

The primary outcome (the ODI score at 12 months post-surgery) will be compared between the two groups. Interlaminar full-endoscopic discectomy will be considered equivalent to microscopic discectomy concerning surgical outcomes if the 95% confidence interval (CI) of the treatment difference value of the Interlaminar full-endoscopic discectomy group is included in the equivalence limit of 12.8 points.

To analyze the time-dependent change in secondary patient-reported and clinical outcomes (i.e., VAS pain scores for the back and lower extremities and ODI, EQ-5D, and POSAS scores), a linear mixed model repeated-measures analysis of variance will be used. Time will be regarded as a categorical variable (at 2 weeks and at 3, 6, and 12 months) and analyzed to evaluate serial changes from baseline, within each group, and between the two groups at each session, with a post hoc test used for any significant time- and group-differences identified.

Chi-square test for categorical variables and Student’s t-test for continuous variables will be used to analyze other clinical and radiographic outcomes and adverse effects between the two groups. The collected data’s distribution will be evaluated using the Shapiro–Wilk test, with a two-sided P-value. Normally distributed continuous variables will be reported as means and standard deviations (SDs), with non-normally distributed continuous variables reported as medians and interquartile ranges. Categorical variables will be reported as count and percentage (%).

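### The stated 50 per group does not follow from the stated sample-size inputs, and the 95% CI equivalence rule in the analysis section matches neither the planned one-sided interval nor the non-inferiority hypothesis

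*Protocol article*

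**What the plan says.** In the protocol article, the Background and Trial design sections describe a non-inferiority trial. Sample size justification does the same: "the non-inferiority margin is 12.8 points", "with an SD of 17.1 points at 1-year after endoscopic discectomy", and then "50 participants will be required in each group, with an alpha value of 0.05, a power of 0.90, a one-sided 95% CI", with 20% loss to follow-up. It states no assumed true difference between the arms.

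Statistical analyses also calls the trial a non-inferiority RCT, but gives its primary criterion in equivalence terms. Endoscopic discectomy is to be declared equivalent "if the 95% confidence interval (CI) of the treatment difference value" falls inside an equivalence limit of 12.8 points. The interval is not labelled one-sided or two-sided.

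**The concern.** There are two linked problems.

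- **The number and its inputs disagree.** "with an alpha value of 0.05" together with "a one-sided 95% CI" means a one-sided 5% test. For the stated margin, SD, power and loss, that test calls for clearly fewer than 50 per group unless a non-zero true difference was assumed. A reader cannot tell which error rate, hypothesis or assumed difference the trial was sized for.
- **The planning interval and the decision interval disagree.** A one-sided 95% bound is the limit of a two-sided 90% CI. A 95% CI that must lie within a limit is ordinarily two-sided, and containment is an equivalence requirement, not a non-inferiority one.

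At stake is the primary conclusion. The choice of interval decides some plausible results, and the choice between equivalence and non-inferiority decides whether the planned number delivers the planned power. Neither should be open once data are seen.

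**Working it through.** **Inputs.** From Sample size justification: margin M = 12.8, SD = 17.1, alpha = 0.05 with a one-sided 95% CI, power 0.90, loss 20%. From Randomization and follow-up: 1:1 allocation. Assumed here: true difference d = 0, the usual default and in line with the Background's expectation of similar results.

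**Formula.** Evaluable per group, normal approximation: n = 2 × (z(1−alpha) + z(power))² × SD² / (M − d)². The exact noncentral-t calculation adds about one per group. Enrolled = n / (1 − 0.20).

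**1. As written (non-inferiority, one-sided 0.05, d = 0).** 2 × (1.645 + 1.282)² × 17.1² / 12.8² = 30.6, so 31. Exact t gives 32 (power 90.6%). Enrolled: 32 / 0.8 = 40. The stated figure is 50.

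**2. What does give about 50.**

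| Basis | Evaluable per group (exact t) | Enrolled per group |
|---|---|---|
| Non-inferiority, one-sided 0.025, d = 0 | 39 (normal: 37.5, so 38) | 48.75, so 49 |
| Equivalence, two one-sided tests at 0.05 each (90% CI within ±12.8), d = 0 | 40 | 50 |
| Non-inferiority, one-sided 0.05, d = 1.5 in favour of microscopy | 40 | 50 |

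For the last row, M − d = 12.8 − 1.5 = 11.3. The normal approximation is 2 × (1.645 + 1.282)² × 17.1² / 11.3² = 39.2, so 40, and exact t also gives 40. The result is sensitive to d: 1 point gives 37 evaluable (46.25, so 47 enrolled) and 2 points gives 44 (55 enrolled).

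**3. Power with 40 evaluable per group** (50 less 20%), d = 0, exact t.

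- Non-inferiority, one-sided 0.05: 95.3%.
- Non-inferiority, one-sided 0.025: 91.1%.
- Equivalence, 90% CI within ±12.8: 90.6%.
- Equivalence, two-sided 95% CI within ±12.8: 82.2% (normal approximation 83.5%). Power of 90% would need 48 evaluable and 48 / 0.8 = 60 enrolled per group.

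**4. Where the interval changes the verdict.** SE = 17.1 × √(2/40) = 3.82, with 78 degrees of freedom.

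- One-sided 95% bound: half-width 1.665 × 3.82 = 6.36. The largest observed endoscopic disadvantage that passes is 12.8 − 6.36 = 6.4 points.
- Two-sided 95% CI: half-width 1.991 × 3.82 = 7.61. The largest that passes is 12.8 − 7.61 = 5.2 points.

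An observed disadvantage between about 5.2 and 6.4 points passes under one interval and fails under the other.

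**The case against.** The strongest reply has four parts.

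- **The 40 rests on an unstated input.** A non-inferiority calculation needs a true difference and the article gives none. With 1.5 points the stated alpha, sidedness and hypothesis reproduce 50 exactly, and a condensed article may leave such a software input to the full protocol. This stands: 40 is conditional on a difference of 0, and a flat claim that 50 is wrong would go too far. It does not remove the point, because the article says that 50 are required on the inputs it lists, and the only expectation it voices is similarity.
- **The mismatch is conservative.** This also stands. A reader might infer that enrolment should fall to 40 per group, or that this calculation leaves the trial short of power for non-inferiority. Neither is supported: with 40 evaluable and a true difference of 0, power exceeds 90% at either one-sided level.
- **There are not two rival decision rules.** Correct. Sample size justification lists planning inputs, and the only success criterion is in Statistical analyses. That criterion does not print two-sided, so it is tempting but too strong to say that the article fixes a 5% false-positive rate in one place and 2.5% in the other. The 2.5% depends on the ordinary reading of an unlabelled 95% CI. The two sections could be read together as one-sided, but containment within an equivalence limit fits that reading badly.
- **The analysis plan will settle it.** A later document can supply what is missing. Here the article states both a planning basis and a decision rule, and on the ordinary reading they disagree, so a later plan could agree with only one.

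**Conclusion.** The point holds in a limited form. With a true difference of 0, the stated inputs lead to 32 evaluable and 40 enrolled per group, against a stated 50. Because several neighbouring specifications give 49 or 50, the misdescription is probably in the alpha, the sidedness, the hypothesis or the assumed difference, not in N. The documents do not show which.

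The more consequential part is the decision rule. A 95% CI inside an equivalence limit matches neither the planned one-sided 95% CI nor the non-inferiority aim. For an observed endoscopic disadvantage of about 5.2 to 6.4 points, the primary conclusion depends on which interval is used. If the rule means a two-sided 95% CI within ±12.8, power is about 82%, below the planned "a power of 0.90".

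These figures assume an SD of 17.1 in both arms, 40 evaluable per group and, for sample size and power, a true difference of 0. The reading of the 95% CI as two-sided is the ordinary one, not one the article prints.

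**What to change.** Make the two sections state one hypothesis, one alpha with its sidedness, and the matching interval.

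1. **Sample size justification:** non-inferiority; one-sided alpha 0.025 (upper limit of the two-sided 95% CI); assumed true difference 0; SD 17.1; margin 12.8; power 0.90. This gives 39 evaluable per group, 49 with 20% loss, rounded to 50.
2. **Statistical analyses:** replace the equivalence rule with: non-inferiority is concluded if the upper limit of the two-sided 95% CI for the ODI difference at 12 months (endoscopic minus microscopic) is below 12.8.

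Both edits are needed. Correcting the alpha while leaving the equivalence wording would keep the power problem.

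The cost is two sentences and a stricter stated alpha. Enrolment stays at 100, with 91.1% power at 40 evaluable per group. If the sponsor does intend equivalence with a two-sided 95% CI, the article should say so throughout and restate the power as about 82%; keeping 90% would take about 60 enrolled per group.

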## Discussion

Previous studies have reported that interlaminar full-endoscopic discectomy offers similar clinical outcomes but is less invasive compared to open microscopic discectomy [18–22]. However, evidence supporting the efficacy and safety of interlaminar full-endoscopic discectomy is limited by the type of research design previously applied, i.e., retrospective, single-center prospective designs [7, 18–25].

This trial will be the most valuable, multicenter, prospective RCT to evaluate and to comparatively analyze the efficacy, safety, and applicability of interlaminar full-endoscopic discectomy, compared with those of open discectomy, in patients with lumbar disc herniation. The quality of the evidence will be improved by adequate sample size, blinded assessments, and prospective registration from multiple centers to reduce bias. This will ensure that the two approaches are evaluated equivalently. We anticipate that this high-quality evidence will provide a clear conclusion on the efficacy and safety of interlaminar full-endoscopic discectomy as an alternative option, with the same surgical outcome and less invasiveness, for the treatment of lumbar disc herniation.

## Data Availability

The electronic database server (iCReaT) will not be publicly accessible. Access to the data set is provided only to the Data Management Committee of the Korean Government Research Consortium. The study findings will be published in a peer-reviewed journal.

## Abbreviations

CI: Confidence interval
CT: Computed tomography
eCRF: Electronic case report file
EQ-5D-5L: EuroQol 5-dimension 5 level
iCReaT: Internet-based clinical research and trial
MR: Magnetic resonance
ODI: Oswestry Disability Index
POSAS: Patient and Observer Scar Assessment Scale
QOL: Quality of life
RCT: Randomized controlled trial
SD: Standard deviation
VAS: Visual analog scale
